**Study synopsis**

| **Name of investigational treatment**  Cabergoline 0.5 mg once weekly |
| --- |
| **Title of study**  Cabergoline as a Preventive Treatment for Migraine: An Investigator-Initiated, Randomized, Clinical Trial |
| **Sponsor**  [name], Professor, Dr.Med., MD, Department of Clinical Medicine, Aarhus University, Department of Endocrinology, Aarhus University Hospital. |
| **Coordinating Investigator**  [name] [name], PhD, Steno Diabetes Center Aarhus, Aarhus University Hospital, Denmark, Dept. of Clinical Pharmacology, Aarhus University Hospital, Denmark. |
| **Collaborators**   - [name], Dr.Med., MD   Department of Clinical Medicine, Aarhus University   - [name] [name], Dr.Med., MD   Department of Clinical Medicine, Aarhus University   - Associate professor [name], Dr.Med., MD   Neurology Department, Aarhus University Hospital   - [name], Dr.Med.   Steno Diabetes Centre, Aarhus, Aarhus University Hospital. |
| **Study center**  Aarhus University Hospital |
| **Objectives**   To compare cabergoline 0.5 mg once weekly with placebo in the preventive treatment of migraine in a single center, prospective, randomized, placebo-controlled clinical trial. |
| **Methodology**  Following informed consent, participants are randomized in a 1:1 fashion to cabergoline 0.5 mg once weekly or placebo for 12 weeks. |
| **Number of subjects**  36 |
| **Inclusion criteria**  Patients with migraine and more than 6 migraine days per month  and  ≥18 years of age.  and  written informed consent. |
| **Exclusion criteria**   - Known or suspected heart valve disease - Severe untreated hypertension - Treatment-requiring psychiatric diagnosis - Treatment with dopamine receptor agonists - Treatment with medications known to interact with Cabergoline (dopamine D2 receptor antagonists, macrolides, and itraconazole) - Pregnant or breastfeeding women - According to Investigator discretion individuals deemed unlikely to comply with prescribed study procedures, restrictions, or prerequisites will be excluded. Additionally, the Investigator possesses the authority to identify and exclude, at their discretion, any conditions that may render a participant's involvement in the study unsafe or inappropriate. |
| **Primary outcome measure**  Change in Monthly Migraine Days (MMD) between the baseline period and the final 28 days of the treatment period. |
| **Secondary outcome measures**   - ≥ 50% reduction in MMD - PGIC (Patients Global Impression of Change) measured on a numerical rating scale 0-10 (Likert scale 0-10; where 0=very much worse, 10=very much better, 5=no change) - use of acute migraine–specific medication (triptans) - change from baseline in MIDAS score and HIT-6 score |
| **Exploratory outcome measure**  Change in serum prolactin level from baseline |
| **Safety**  To ensure participant safety, phone calls are scheduled after four and eight weeks, specifically inquiring about side effects. Throughout the trial and up to four weeks after, participants can contact one of the trial coordinators if they experience any side effects from the trial medication. |

**1. Abbreviations**

CGRP neuropeptide calcitonin gene-related peptide

HIT-6 headache impact test

MIDAS migraine disability assessment score

MMD monthly migraine days

PGIC patient global impression of change

**2. Study rationale**

**2.1 Background**

Headache, including migraine, is a significant health burden both in Denmark and globally[1, 2]. In Denmark, the estimated lifetime prevalence of migraine is up to 25%. The disease often affects individuals in the working age and is more frequent in women [3, 4]. Migraine is characterized by episodic and unilateral headache, often accompanied by nausea, sensitivity to light and sound, and sometimes aura [5]. The headache lasts between 4 and 72 hours, and a large portion of patients experience recurrent attacks with a frequency of more than eight days per month [6].

**2.2. Pathogenesis of migraine**

The etiology of migraines remains incompletely elucidated; however, the trigeminovascular system, comprising trigeminal neurons and their innervated blood vessels, is deemed pivotal due to the activation and sensitization of afferent neurons with cell bodies situated in the trigeminal ganglion [4, 7, 8]. This activation subsequently engages second-order neurons within the brainstem, encompassing the trigeminocervical complex, and third-order neurons within the thalamus. Nociceptive impulses are then projected to the somatosensory cortex and other cortical regions implicated in pain perception. Concurrently, the release of vasoactive peptides and signaling molecules ensues, inducing local inflammation and dilation of intracranial arteries. Notably, neuropeptide calcitonin gene-related peptides (CGRP) play a significant role in this activation [4]. Preclinical data further propose that activation of the trigeminovascular system leads to parasympathetic outflow to intracranial arteries, including the dural arteries, via the superior salivatory nucleus and the sphenopalatine ganglion. This contributes to the release of diverse signaling molecules, culminating in the dilation of intracranial arteries [4].

**2.3 Treatment of migraine**

The pharmacological management of migraine encompasses acute and preventive strategies, often necessitating a combination of both [9]. Triptans, which selectively activate serotonergic 5-HT1B and 5-HT1D receptors, constitute the primary medications for acute treatment [10]. In the realm of preventive treatment, commonly employed agents include beta-blockers, angiotensin II antagonists, and antiepileptics. Notably, novel therapeutic approaches involve the use of human antibodies targeting calcitonin gene-related peptide (CGRP) and the CGRP receptor, demonstrating efficacy in both acute and preventive settings [11]. Treatment with CGRP antibodies, however, carries a substantial economic burden, and consequently, their utilization in Denmark is limited to prophylactic treatment for chronic migraine in adults, specifically following inadequate response to previous preventive therapies.

**2.4 Cabergoline**

Cabergoline is a dopamine receptor agonist with prolactin-inhibiting effects. Cabergoline has been used for decades and is approved for the treatment of hyperprolactinemic conditions, including prolactin-producing pituitary tumors, inhibition of lactation, gynecomastia, and acromegaly. abergoline is also indicated for the treatment of Parkinson's disease. In addition to its role as a dopamine receptor agonist, cabergoline also exhibits agonistic effects on several serotonin receptors, including 5-HT1B and 5-HT1D [12].

**2.5 Migraine and cabergoline**

In an observational study of patients with hyperprolactinemia and concurrent headaches, cabergoline demonstrated a significant and notable positive impact on headache symptoms [13].

The involvement of dopamine in the pathophysiology of migraine is a subject of ongoing debate [14, 15]. On one hand, dopamine receptor antagonists, such as metoclopramide and domperidone, find application as antiemetics in the acute treatment of migraine, and certain prodromal symptoms are believed to be dopamine-mediated [15]. On the other hand, clinical evidence suggests the efficacy of dopamine receptor agonists, such as bromocriptine, in migraine treatment [16-18]. This aligns with findings indicating that dopamine inhibits nociceptive signals within the trigeminocervical complex in rodent models [19, 20].

Furthermore, dopamine exerts inhibitory effects on the secretion of the pituitary hormone prolactin, and cabergoline and other dopamine receptor agonists, such as bromocriptine, are indicated for treatment of hyperprolactinemia. Prolactin is suggested to be associated with migraines. Rodent experiments propose that prolactin enhances excitability in neurons originating from the trigeminal ganglion, potentially via the CGRP system [21, 22]. Elevated prolactin levels have been observed in female migraine patients [23]. Additionally, hyperprolactinemia, commonly linked to a prolactin-producing pituitary adenoma, frequently coexists with headaches, including migraines [24].

**2.6 Purpose**

In a randomized, placebo-controlled pilot study, we aimed to investigate the effects of cabergoline treatment in patients with migraines experiencing more than six headache days per month compared to placebo.

**3. Methods**

**3.1.1 Design**

This trial is a prospective, randomized, double-blind, placebo-controlled pilot study testing the hypothesis that in patients with migraine, cabergoline 0,5 mg weekly will reduce number of monthly migraine days (MMD) more effectively than placebo. Participants will be randomized to treatment with cabergoline 0.5 mg once weekly or placebo in addition to any existing migraine treatment and followed up after three months (12 weeks) of intervention.

**3.1.2 Randomization**

Thirty-six patients will be randomized to receive treatment with 0.5 mg Cabergoline or placebo once a week. The randomization is conducted in a 1:1 ratio in 2 blocks of 18 patients and performed by the Aarhus University Hospital Pharmacy. The corresponding order of numbering and treatment assignment is specified in a randomization list, which is kept at the Service Production Hospital Pharmacy throughout the entire process. The Hospital Pharmacy also labels both the investigational drug and the placebo. Along with the investigational drug, the Hospital Pharmacy provides sealed code envelopes (corresponding to the randomization) that can be broken for individual participants if it is necessary for the investigator to know the assigned treatment.

**3.1.3 Study program**

The study consists of a 4-week baseline period during which participants will fill out a daily electronic headache diary, first visit (day 1) comprising 2 x questionnaires and blood samples, 12 weeks treatment period during which participants will fill out a daily electronic headache diary, followed by the last visit comprising 2 x questionnaires, PGIC and blood samples. To ensure participant safety and promote compliance, participants will be contacted by phone after four and eight weeks.

**3.1.4 Study medication**

Cabergoline: Cabergoline "Teva," tablets 0.5 mg. Should not be stored at temperatures exceeding 30 °C. Placebo: Placebo tablets, 6 mm. No specific storage conditions.

If a participant forgets to take the investigational medication, the tablet is taken as soon as possible, up to three days after the scheduled time. Any excess medication is subsequently returned to the study coordinator for counting. Unused/expired investigational medication is destroyed.

**3.1.5 Blood sample**

Blood samples are taken on day 1 and after 12 weeks. A maximum of 30 ml of blood is taken at a time. Bruising may occur after blood sampling. Infection is extremely rare.

**3.2 Patients**

A total of 36 patients with more than six migraine days per month and with stable migraine treatment will be included in the study.

**3.2.1 Patient recruitment and inclusion**

Participants will be recruitment from the Department of Neurology, Aarhus University Hospital. Additionally, recruitment happen via the official Facebook page of Aarhus University Hospital. Potential participants receive participant information and will subsequently be contacted by the coordinating investigator by phone or email, with their permission.

- - 1. **Inclusion criteria**
- Patients with migraine and more than 6 migraine days per month
- Male or female subjects ≥18 years of age
- Written informed consent.

**3.2.3 Exclusion criteria**

- Known or suspected heart valve disease
- Severe untreated hypertension
- Treatment-requiring psychiatric diagnosis
- Treatment with dopamine receptor agonists
- Treatment with medications known to interact with cabergoline (dopamine D2 receptor antagonists, macrolides, and itraconazole)
- Pregnant or breastfeeding women.
- According to Investigator discretion individuals deemed unlikely to comply with prescribed study procedures, restrictions, or prerequisites will be excluded. Additionally, the Investigator possesses the authority to identify and exclude, at their discretion, any conditions that may render a participant's involvement in the study unsafe or inappropriate.

**3.2.4. Dropout**

Participants can withdraw from the trial at any time without consequences for their future treatment. Data obtained from a withdrawn participant will be utilized, if possible – it depends on when in the study a given participant withdraws. Patients will be withdrawn from the study if:

- The participant wishes to withdraw.
- The investigator determines that the participant cannot adhere to the trial procedures.
- The participant develops severe or intolerable side effects. In such cases, the trial will be stopped for the individual participant, and the investigator will arrange relevant follow-up, including referral for appropriate treatment.
- Conditions arise as described under 'Exclusion Criteria'.
- Changes in the established migraine treatment.
- Pregnancy.

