**3.4.1 Cabergoline**

I this trial, participants randomized to cabergoline treatment will recieve 0.5 mg/week, totaling 6 mg throughout the trial period. Cabergoline side effects are dose-dependent. According to the product summary, the following side effects have been reported:

Very common (> 10%): Nausea, dyspepsia, gastritis, abdominal pain, fatigue, headache, dizziness.

Common (1 - 10%): Constipation, vomiting, depression, asymptomatic hypotension.

In extremely rare cases, fibrotic diseases, including pericardial and pulmonary fibrosis, have been reported, and a possible association between Cabergoline treatment and fibrotic heart valve disease has been suggested. The association has been observed in Parkinson's patients of advanced age and comorbidity after prolonged high-dose treatment (3 mg/day for more than 6 months ≈ 540 mg). The accumulated dose in this project is 6 mg. Recently, the British Society of Echocardiography, the British Heart Valve Society, and the Society for Endocrinology, based on a review of existing literature, concluded that there is extremely limited evidence that treatment with dopamine receptor agonists at doses used in the treatment of hyperprolactinemia can cause heart valve disease [25].

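### Section 3.2.4 withdraws participants from the study, not only from study drug, for reasons plausibly linked to outcome and arm, so the primary outcome can go uncollected in an informative way

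*Protocol*

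**What the plan says.** Section 3.2.4 (Dropout) opens its list of triggers with "Patients will be withdrawn from the study if". Three of them matter here:

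- Side effects: "The participant develops severe or intolerable side effects. In such cases, the trial will be stopped for the individual participant". The follow-up then arranged is clinical. Continued outcome collection is not mentioned.
- Any emerging exclusion condition. Under section 3.2.3 these include "Treatment with medications known to interact with cabergoline (dopamine D2 receptor antagonists, macrolides, and itraconazole".
- "Changes in the established migraine treatment".

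Just before the list, the section says that a withdrawn participant's data will be used where possible, depending on when the withdrawal happens. No section defines a status of being off study drug but still in follow-up.

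Section 3.1.3 has a daily electronic diary through the 4-week baseline and 12-week treatment periods, then a last visit. Section 3.3.1 defines the primary endpoint as the change in monthly migraine days from baseline to the final 28 treatment days. Section 4.2 plans a modified intention-to-treat analysis of everyone randomised and treated, with censoring at withdrawal of consent or, for those lost to follow-up, at the last visit.

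**The concern.** A patient whose migraine is poorly controlled may have treatment stepped up, and that change ends participation. A patient who cannot tolerate the tablets is also withdrawn. The first reason may track the outcome and the second may track the arm, since section 3.4.1 lists for cabergoline "Very common (> 10%): Nausea, dyspepsia, gastritis, abdominal pain, fatigue, headache, dizziness". A possible third route combines the two. Section 2.5 notes that "dopamine receptor antagonists, such as metoclopramide and domperidone, find application as antiemetics in the acute treatment of migraine", and treatment with D2 antagonists is an exclusion condition and hence a withdrawal trigger.

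If those who leave differ in outcome from those who stay, and differ by arm, the comparison over weeks 9 to 12 is no longer the randomised one. A statistical analysis plan can choose how to handle missing values. It cannot recover diary days that were never collected, so the matter belongs in the protocol.

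**Working it through.** **1. When the endpoint is lost.** Treatment lasts 12 × 7 = 84 days, so the primary window is days 57 to 84 (weeks 9 to 12). Withdrawal before day 57 leaves no diary day in the window; withdrawal on days 57 to 84 leaves part of it. The provision to use data where possible covers only what has already been obtained.

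**2. The plan's own numbers.** Section 4.3 cites a rule of thumb of 30 participants, a maximum dropout of 20%, and 18 per arm (36 in total).
- 30 × 1.20 = 36 reproduces the stated total; 30 / (1 − 0.20) = 37.5, rounded up to 38, is close to it.
- At the full 20% loss, 36 × 0.80 = 28.8 remain, or 14.4 per arm.

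This allowance deals with how many are lost. It does not deal with which participants are lost.

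**3. Illustration of the bias.** The protocol states no SD, no dropout by arm and no link between withdrawal and outcome, so these inputs are assumptions:
- true difference of 0;
- SD of the change 4 days (range 3 to 5);
- 20% withdrawn in each arm;
- withdrawal in the placebo arm correlated ρ with a poor outcome, and unrelated to outcome in the cabergoline arm.

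The shift in the completers' mean is ρ × SD × φ(z) / (1 − p), where p is the proportion withdrawn and z the matching normal quantile. For p = 0.20, φ(z)/(1 − p) = 0.350.

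| ρ | Bias, SD 4 (days) | Two-sided type I error (nominal 5%) |
| --- | --- | --- |
| 0 | 0 | 5.0% |
| 0.3 | 0.3 × 4 × 0.350 = 0.42 | 5.7% |
| 0.5 | 0.5 × 4 × 0.350 = 0.70 | 7.4% |
| 1.0 | 1.0 × 4 × 0.350 = 1.40 | 16.6% |

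The error rates come from 40,000 simulated trials with 18 randomised per arm and an unpaired t-test on completers. The row for ρ = 1.0 means that exactly the worst 20% leave one arm. It is a ceiling for this SD and dropout, not an expectation.

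**4. Sensitivity at ρ = 0.5.** With 20% outcome-related withdrawal, the bias is 0.52 days at SD 3 and 0.87 at SD 5. With 10%, φ(z)/(1 − p) = 0.195, and the bias is 0.29, 0.39 and 0.49 days at SD 3, 4 and 5.

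**5. Scale.** With SD 4 and 14.4 per arm, the standard error of the difference is 4 × √(2/14.4) = 1.49 days. The middle case, 0.70 / 1.49, is about half a standard error.

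**6. Direction.** In this scenario the placebo completers look too good, so the bias runs against cabergoline. If the outcome-related losses fall in the cabergoline arm instead, the sign reverses.

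**The case against.** Several points on the other side are sound.

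- **Not all dropout comes from these triggers.** The 20% is a maximum over all causes, 0.20 × 18 = 3.6 patients per arm. It includes those who leave by their own wish or cannot follow procedures, and continued follow-up may not recover them. The share due to the three triggers is smaller, so the lower figures are the more relevant ones.
- **Some data survive.** The diary is daily, so pre-withdrawal data exist, and a withdrawal in weeks 9 to 12 leaves part of the window. How to use these may properly be left to an analysis plan. It does not help with a withdrawal before week 9.
- **This is a 36-patient pilot.** That limits the consequence, but sections 3.1.1 and 4.1 still set an efficacy hypothesis and two-sided 5% tests.

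A reader might also infer stronger conclusions that the documents do not support:

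- **That section 3.2.4 contradicts section 4.2.** Section 4.2 counts everyone randomised and treated, and itself foresees withdrawals and losses. Withdrawn patients stay in that population with incomplete data. The withdrawal rule undermines the analysis; it does not contradict it.
- **That worse patients are certain to be removed selectively.** Treatment may also change after improvement, and stopping for nausea need not track migraine days.
- **That one antiemetic dose for one attack ends participation.** Section 3.2.3 speaks of treatment with these drugs and does not say whether a single dose counts. Patients on such treatment at entry are already excluded, and use of triptans for attacks is a secondary endpoint, so treating an attack is not in itself a trigger. The antiemetic route is an inference.
- **That a bias of 1.4 days is to be expected.** It needs perfect correlation and an assumed SD.

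**Conclusion.** The point holds in this form. Section 3.2.4 ends study participation, not only study drug, for three protocol-imposed reasons, and no section continues outcome collection afterwards. This much is read directly from the text. That the loss may be informative is a plausible inference from the nature of the triggers; its direction is uncertain and its size cannot be derived from the protocol.

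Under the stated assumptions the bias is roughly 0.4 to 0.7 days at moderate correlation, with a ceiling of 1.4 days, against a standard error of about 1.5 days. It would be less where these triggers account for only part of the 20%. The flaw is moderate in size and worth correcting because the remedy is cheap and must be in place before the data are lost.

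**What to change.** Amend section 3.2.4 to separate stopping study drug from leaving the study, without altering any clinical rule on when treatment stops. Specifically:

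- Unless the participant withdraws consent to follow-up, the existing electronic diary continues to day 84 and the planned last visit is kept.
- Changes in migraine treatment and use of the listed interacting drugs are recorded with dates.
- The participant stays in the randomised arm for the modified intention-to-treat analysis.
- Whether data after a treatment change enter the primary analysis or a sensitivity analysis is an estimand choice. It should be prespecified, and either option can be defended.

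The cost is a short amendment to section 3.2.4 and to the participant information, with no new visits. A few participants would keep the diary after stopping study drug, and changed background treatment may dilute the contrast if those data are included.

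This removes missing data caused by the protocol's own triggers among participants willing to continue. It does not recover data from those who withdraw consent, for whom collection properly ends.

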**3.3 Endpoints**

**3.3.1 Primary endpoint**

The primary endpoint was change in MMD between the baseline period and the final 28 days of the treatment period. A migraine day is defined as any calendar day on which the participant has onset, continuation, or recurrence of migraine as recorded in the electronic diary. MMD was defined as number of migraine days per 28 days.

**3.3.2 Secondary endpoints**

- ≥ 50% reduction in MMD
- Patient global impression of change (PGIC) measured on a numerical rating scale 0-10 (Likert scale 0-10; where 0=very much worse, 10=very much better, 5=no change)
- use of acute migraine–specific medication (triptans)
- change from baseline in MIDAS score and HIT-6 score

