**4.1 Statistical analysis**

Differences between study groups will be assessed with unpaired t-tests or using non-parametric statistics as appropriate. Ordinal variables will be assessed with chi-2 test for trend or Mann-Whitney U test and Pearson’s chi-square test or Fisher's exact test will be used to test differences between proportions. Two-sided statistical significance levels of 5% will be used and estimates will be presented with 95% confidence intervals.

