**4.3 Sample size calculation**

We have not identified any previous randomized studies investigating the use of cabergoline in patients with migraine. Here we conducted a pilot study. The sample size should be large enough to provide meaningful feedback and detect potential problems, and reflect the diversity and characteristics of the target population. A common rule of thumb is to use a sample size of at least 30 participants. Due to the short duration of the study, we expect a maximum dropout rate of 20%. We will therefore include 18 patients in each intervention group.

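### Triptan use is listed as a bare level and tested without baseline adjustment, which costs precision at 18 per arm but does not bias the comparison

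*Protocol*

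**What the plan says.** Section 3.3.2 and the synopsis give the acute-medication endpoint as "use of acute migraine–specific medication (triptans", closing the bracket and adding nothing more. The next bullet in the same list is "change from baseline in MIDAS score and HIT-6 score", and the primary endpoint in section 3.3.1 is "change in MMD between the baseline period and the final 28 days of the treatment period". The responder outcome is a reduction, PGIC is itself a rating of change, and prolactin in section 3.3.3 is a change. Triptan use is the only one of these outcomes without a reference point.

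On analysis, section 4.1 states "Differences between study groups will be assessed with unpaired t-tests or using non-parametric statistics as appropriate" and "Two-sided statistical significance levels of 5% will be used". It names no covariate.

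On allocation, section 3.1.2 states "The randomization is conducted in a 1:1 ratio in 2 blocks of 18 patients" and describes no stratification. Section 4.3 states "We will therefore include 18 patients in each intervention group".

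On background therapy, section 3.1.1 adds the trial drug "in addition to any existing migraine treatment". The inclusion criteria do not ask for triptan use. Section 3.2 requires migraine treatment to be stable, and section 3.2.4 makes an alteration of it a reason for withdrawal. Section 3.1.3 provides a daily electronic diary over four baseline weeks and twelve treatment weeks.

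**The concern.** As worded, the endpoint could mean the number of users, of days or of doses, over any part of treatment, with or without reference to baseline. Combined with section 4.1, the most direct reading is a plain comparison of on-treatment levels.

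Triptan use is likely to vary widely between patients before treatment. Some may take none and score zero throughout, while others use triptans often. With two arms of 18 and no stratification on this variable, the arms can differ noticeably at entry by chance, and an unadjusted comparison of levels leaves that difference in the result. The four-week baseline period is the obvious source of a value that would remove it. What is at stake is the precision of one secondary endpoint, and the reading of an individual result when the arms happen to start apart.

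**Working it through.** **Inputs from the protocol.** 18 per arm (section 4.3), 1:1 allocation without stratification (3.1.2), two-sided 5% level and unadjusted tests (4.1), 28-day baseline diary (3.1.3).

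**The plan's own figure.** The protocol gives no number for this endpoint. Its total of 36 follows from at least 30 participants and 20% dropout as 30 × 1.2 = 36. Dividing instead gives 30 / 0.8 = 37.5, rounded up to 38. The calculation below takes 18 per arm as stated.

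**Assumption.** The protocol gives neither an SD nor a correlation for triptan use. Results are therefore in SD units, with equal variance at baseline and follow-up, and ρ ranges from 0.3 to 0.8.

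**Step 1: chance difference at baseline.** SE = √(2/n) = √(2/18) = 0.333 SD, and 1.96 × 0.333 = 0.653 SD. The probability of a gap above 0.5 SD in either direction is 2[1 − Φ(0.5/0.333)] = 13%. With 15 per arm, SE = √(2/15) = 0.365 SD and the probability is 17%.

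For scale only, assume that 60–80% of patients are users, with mean 5 and SD 2.5, or mean 7 and SD 3, triptan days per 28 days among users. The variance is u(s² + m²) − (um)², which gives an overall SD of 3.00 to 4.14 days. The SE of the chance difference is then 1.00 to 1.38 days, and its 95% range is ±1.96 to ±2.71 days.

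**Step 2: three ways to analyse the endpoint.**

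- Follow-up level only: SE = √(2/n)
- Unadjusted change score: SE = √(2/n) × √(2(1 − ρ))
- Baseline as covariate (ANCOVA): SE = √(2/n) × √(1 − ρ²)

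At ρ = 0.6, for example, the change score gives 0.333 × √0.8 = 0.298 and ANCOVA gives 0.333 × √0.64 = 0.267. Power is for an assumed true effect of 0.8 SD, by normal approximation.

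| ρ | Baseline share of level variance, ρ² | SE level | SE change | SE ANCOVA | Power level / change / ANCOVA |
|---|---|---|---|---|---|
| 0.3 | 9% | 0.333 | 0.394 | 0.318 | 67% / 53% / 71% |
| 0.5 | 25% | 0.333 | 0.333 | 0.289 | 67% / 67% / 79% |
| 0.6 | 36% | 0.333 | 0.298 | 0.267 | 67% / 77% / 85% |
| 0.7 | 49% | 0.333 | 0.258 | 0.238 | 67% / 87% / 92% |
| 0.8 | 64% | 0.333 | 0.211 | 0.200 | 67% / 97% / 98% |

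The change score beats the level only when 2(1 − ρ) < 1, that is, when ρ > 0.5. The ANCOVA formula is below 1 for every ρ above zero. It ignores the estimation of the slope, which multiplies the variance by about 1 + 1/(36 − 4) = 1.031. At ρ = 0.3 the product is 0.91 × 1.031 = 0.94, still below 1; the advantage disappears only when ρ² is below about 0.03.

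**Step 3: what one unlucky allocation does.** A baseline gap of d shifts the expected difference in levels by ρd. For d = 0.5 SD this is 0.15 SD at ρ = 0.3, rising to 0.40 SD at ρ = 0.8. Given such a gap, with s = 0.333, the two-sided type I error is 1 − Φ[(1.96s − ρd)/(s√(1 − ρ²))] + Φ[(−1.96s − ρd)/(s√(1 − ρ²))]. This is 6% at ρ = 0.3 and 10% at ρ = 0.8. Over all randomizations the gap averages to zero and the error rate is the nominal 5%.

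**The case against.** The strongest reply is that section 3.3.2 is a short list that names variables, and that window, unit and covariates of a secondary endpoint normally belong in the SAP, which is not shown. That is fair as far as it goes: an SAP may already settle this. But the protocol does say how groups will be compared, and it names unadjusted tests. It also attaches a reference point to every neighbouring outcome and not to this one. A change to the wording is justified on that evidence.

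A second reply is that chance imbalance in a randomized trial is noise already reflected in the standard error. This stands, and it limits the point to precision.

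Three stronger readings are tempting, and the documents do not support them.

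- A reader might infer that the result would mostly reflect who used triptans at entry. The baseline share is ρ², which passes one half only at the top of the assumed range. The protocol gives no effect size against which to rank it.
- A reader might infer that switching to another acute drug would simply count as improvement. Sections 3.2 and 3.2.4 require stable treatment and withdraw patients whose established treatment is altered. What stays unclear is whether taking, say, a simple analgesic in place of a triptan for a single attack falls under that rule. In a double-blind trial nothing in the protocol suggests that this would differ by arm. The restriction to triptans is also a stated choice, since the endpoint is labelled migraine-specific.
- A reader might infer that the primary result is weakened. The protocol gives triptan use no role in interpreting migraine days.

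**Conclusion.** The point holds as a matter of definition and efficiency. The endpoint lacks a reference, a window and a unit, and the stated tests leave unused a baseline period that could sharpen the comparison. The loss is a share ρ² of the variance, 9% to 64% over the assumed range of ρ. For an assumed 0.8 SD effect, baseline adjustment would raise power from 67% to between 71% and 98%. These figures rest on equal variances and an assumed correlation, because the protocol supplies neither. There is no bias, no stated number changes, and the endpoint is one secondary outcome of a trial that calls itself a pilot. It is a modest improvement worth making, not a defect that threatens the trial's conclusions.

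**What to change.** In section 3.3.2 and the synopsis, define the endpoint as the number of days with triptan use per 28 days, from the diary, in the last 28 days of treatment compared with the 28-day baseline period. In section 4.1, state that it is analysed by ANCOVA with the baseline value as covariate. The adjusted treatment difference is the same whether the outcome is entered as a level or as a change. An unadjusted t-test on levels or on change scores should not be the main analysis. If many patients report zero days, a rank-based comparison can serve as a sensitivity analysis.

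The cost is a line of wording and a negligible amount of analysis work, assuming that the diary already records triptan days, which the protocol does not say. If it does not, one daily item is needed from the start of the baseline period, because baseline use that was never recorded cannot be recovered reliably.

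Reporting days with any acute headache medication alongside is optional. It would make single-attack substitution visible, at the price of one more reported outcome and possibly one more diary item.
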